#### Sleep quality

Sleep quality will be measured by (1) daily patient/nurse-rated sleep assessment (Richards-Campbell Sleep Questionnaire) while in ICU [46] and (2) patient-rated sleep quality questionnaire after ICU discharge [47]. This will be performed from 2 to 14 days after ICU discharge with the timing dependent on the patient’s ability to participate. Patients unable to participate will be omitted.

A subgroup of 100 patients will undergo sleep quality assessments twice during their ICU stay using polysomnography. The hypothesis is that melatonin will increase the quality and quantity of sleep compared with placebo. These 100 patients will come only from either Sir Charles Gairdner Hospital or John Hunter Hospital. Patients included in the study at these sites will be sequentially allocated to the subgroup. Polysomnography will be done between days 2 and 3 and between days 5 and 7 of the ICU stay. For logistical reasons, we will have limited access to polysomnography. It will be available only from Monday through Thursday, and hence we have not been able to randomise patients to this investigation. It is expected that, by virtue of blinding and randomisation, approximately 50% of patients will be from the melatonin arm and 50% from the placebo arm. The polysomnography protocol and reporting have been standardised and agreed upon by senior sleep physicians at the two main centres. Patients will not be in a single room every time polysomnography is performed, because this is a pragmatic study and will reflect real-world conditions as much as possible. Many participating units do not have single rooms for all of their patients. The range of days is selected so that if patients cannot undergo polysomnography because of procedures, they could have it the following night. If polysomnography needs to be aborted, we will try to repeat it within that range of days. This will aid in the understanding of sleep patterns in the critically ill and the biological mechanisms through which melatonin may work.

Several parameters will be generated by the sleep studies. Two sleep experts involved in the study design have selected the following four variables as the most important (each will be a secondary outcome): (1) total sleep time, (2) sleep efficiency, (3) percentage REM sleep and (4) arousal index.

#### ICU and hospital length of stay

ICU and hospital length of stay will be recorded using existing hospital patient data programmes linked to medical records.

#### Morbidity and mortality

Standard ICU markers of morbidity and mortality will be recorded on a daily basis until ICU discharge or day 14 after enrolment. These include (1) duration of mechanical ventilation measured as ventilator-free days; (2) daily need for vasopressor use; (3) daily need for renal replacement therapy; (4) re-intubation, delayed extubation or need for tracheostomy; (5) Sequential Organ Failure Assessment score for injury severity; (6) mortality at 28 and 90 days; and (7) destination after ICU discharge.

#### Healthcare costs

A medical economist will perform a cost-consequence analysis based on LOS and intensity of medical therapy while in ICU.

### Participant timeline and recruitment

Patients will be screened on the morning handover for eligibility. Baseline data will be recorded on day 0. Patients will be assessed each day and have the primary and secondary outcomes recorded daily until ICU discharge or day 14 after enrolment. Patients will be seen on the ward between days 2 and 14 after ICU discharge to complete the sleep questionnaire. Patients who have been discharged home will be contacted by phone. Patients will be followed through their hospital stay to record ICU LOS, hospital LOS, and 28- and 90-day mortality. The trial assessment schedule is displayed in Table 1 and Fig. 1.

**Table 1 Tab1:** Time schedule of Pro-MEDIC enrolment, interventions and assessments

	Day 1	Day 2	Day 3	Day 4	Days 5–14	Days 2–14 post-ICU discharge	Hospital discharge	Days 28 and 90
Inf`ormed consent	X							
Demographic information	X							
Medical co-morbidities	X							
Psychiatric history	X							
Liver function tests	X				X (days 0, 5 and 10)			
CAM-ICU score	X	X	X	X	X			
CAM-S test (for patients found to be delirious)	X	X	X	X	X			
Record daily ICU interventions	X	X	X	X	X			
Record daily anti-psychotic and sedation use	X	X	X	X	X			
Record daily sleep aid measures	X	X	X	X	X			
RCSQ	X	X	X	X	X			
Use of physical restraints	X	X	X	X	X			
Physiotherapy participation	X	X	X	X	X			
Polysomnography		X			X			
Assessment of sleep quality						X		
ICU and hospital LOS							X	
Hospital discharge destination							X	
Mortality at 28 and 90 days								X

*Abbreviations: CAM-ICU* Confusion Assessment Method for the ICU, *CAM-S* Confusion Assessment Method for delirium severity, *ICU* Intensive care unit, *LOS* Length of stay, *Pro-MEDIC* Prophylactic Melatonin for Delirium in Intensive Care, *RCSQ* Richards-Campbell Sleep Questionnaire

**Fig. 1 Fig1:**
[figure not shown]
Time schedule of Prophylactic Melatonin for Delirium in Intensive Care (Pro-MEDIC) enrolment, interventions and assessments. *CAM-ICU* Confusion Assessment Method for the ICU, *CAM-S* Confusion Assessment Method for delirium severity, *ICU* Intensive care unit, *LOS* Length of stay

To allow for accurate recording of LOS, we will allow for a 6-month period after the last patient is enrolled. If there are patients still hospitalised at that point, the last day of the 6-month period will be recorded to calculate as their last day of hospital admission.

### Sample size

On the basis of two sample size calculations, with an alpha value of 0.05 and a power of 80%, a total of 850 patients will be recruited into the study, with 425 patients in each arm. Estimates of sample size were made on the basis of percentage of delirium-free assessments (the primary outcome). An audit of 100 patients at Sir Charles Gairdner Hospital and John Hunter Hospital was used to obtain preliminary data to guide sample size calculations where an average of 54% of assessments were deemed delirium-free (SD 45%). The research group is aiming to detect a 10% increase in the percentage of delirium-free assessments. This would give us a sample size calculation of 319 per group. Adjustment for a non-parametric test (15%) increases this to 367 per group. It is expected that up to 10% of patients recruited into the study will not be assessable for delirium at any point during the study. To account for this and for missing data/loss to follow-up, the sample size was increased by 15% to 423 patients per group (total rounded to 850). This sample size will also be sufficient to analyse the secondary measures.

To prevent and treat the issue of likely missing data, the follow-up period for the primary outcome is short and data collection is electronic, with out-of-range and missing alerts. There will be documentation of why data are missing. This will help us to formulate reasonable assumptions about observations that are missing [48]. To achieve adequate recruitment numbers, there will be frequent reminders to the participating sites, and progress reports will be scheduled periodically.

### Allocation, randomisation, compliance and blinding

Patients will be randomised to melatonin or placebo in a 1:1 ratio according to a computer-generated randomisation list, stratified by site, with standard block sizes of six. An independent statistician other than the statistician analysing the data will create the allocation sequence. This randomisation list will be provided by the independent statistician directly to the compounding pharmacy. Each patient’s bottle will be labelled with a site-specific randomisation number, which will become that patient’s study number. Study sites will administer the content of the study drug bottles sequentially to patients in the order in which they are included in the study.

Each participating site’s principal investigator or research coordinator will enrol patients. All patients will receive the same interventions, except for the sleep studies, which will be assigned by the principal investigators at the two sites performing sleep studies. A flowchart of enrolment, allocation, follow-up and analysis is shown in Additional file 1.

When a patient is enrolled in the study, ‘Pro-MEDIC study drug’ will be charted on the medication chart. The ICU bedside nurse, using an oral/enteral syringe, will administer the study drug at 21:00 until discharge from ICU or 14 days after enrolment, whichever occurs first.

The study drug will be prepared by a single private compounding pharmacy that currently produces melatonin suspension for the health department and has extensive experience in clinical trials. They will be given the randomisation list and will prepare individual bottles for each patient that will contain an amount of the study drug to last for up to 14 days. Both melatonin and placebo will be made to look and taste the same. The melatonin will be prepared as a 2 mg/ml solution. The drug packs will be shipped from the compounding pharmacy to each of the participating sites, and responsibility will be assigned to the site’s principal investigator.

The shelf life of the melatonin suspension is 12 months. The project manager will co-ordinate with the pharmacy to ensure sites have an adequate supply of the study drug based on recruitment rates. Subjects may withdraw their consent to participate in the study at any time and for any reason.

Compliance will be indicated by the nurse’s signature on the medication chart each day that the study drug is administered to the patient. There will be no restriction or change in the use of any sedative, analgesic or anti-psychotic agents given, but the use of these medications will be recorded.

The patients, the investigators, and the ICU doctors and nurses looking after patients enrolled in the study will be blinded to the treatment that patients are receiving. Only the independent statistician providing the allocation list to the pharmacy, the compounding pharmacy, and the independent data and safety monitoring committee (DSMC), should they need to investigate an adverse event (AE), will know which is melatonin and which is placebo.

A standardised process for unblinding will be in place for all sites. Blinding will be broken only if the senior treating ICU doctor feels that the drug is causing AEs to the patient and it is necessary to know if the patient received melatonin, such as in the case of anaphylaxis. Other AEs may lead to cessation of the study drug but would not be expected to require unblinding.

### Data collection and management

Data will be collected and entered into a REDCap© [49] electronic database behind a secure firewall. The REDCap system will perform data entry validation. For the non-primary sites, data can be entered into the REDCap database, or the case report forms can be filled in manually and forwarded to the primary sites. Strict confidentiality and privacy will be kept at all times. The data will be stored in password-protected files and will be kept for 15 years. The final database will be locked after all information for the last patient has been entered and provided to the statistician.

If a participant withdraws consent, the investigators will ask permission to retain all data collected up to the point of withdrawal and to collect survival status and discharge destination data. If subjects cease the study drug for any reason, data will still be collected and interpreted in an intention-to-treat analysis. The reason for withdrawal will be recorded. No attempt will be made to replace patients who withdraw from the study.

### Statistical methods

Analyses will be conducted on both intention-to-treat and per-protocol bases. All outcomes will be analysed for superiority (two-sided) and considered statistically significant at the 5% level. Baseline data will be recorded and analysed for imbalances between the treatment groups. The primary endpoint, percentage of delirium-free assessments, will initially be analysed using a Mann-Whitney *U* test to compare the two treatment arms. Subsequent supporting analyses will be carried out using a negative binomial model with adjustments made for number of assessments (accounting for withdrawals), important covariates and baseline data where appropriate. Secondary endpoints of any prevalence of delirium during the 14 days and duration of delirium from first onset will be analysed using a chi-square test with supporting analyses of binary and ordinal logistic regression, respectively, allowing adjustments for covariates. Sleep quality analysis based on the Richards-Campbell Sleep Questionnaire on each of days 2–14, the patient-rated sleep questionnaire completed after day 14, and sleep measurements derived from polysomnography done on days 2–4 and 5–7 (total sleep time, sleep efficiency, REM sleep percentage and arousal index) will all be analysed initially using a Mann-Whitney *U* test to compare the two treatment arms and subsequently using linear mixed models with fixed factors of treatment time and their corresponding interaction, along with random patient effects. ICU LOS, total hospital LOS, mortality and morbidity events will be analysed initially using Kaplan-Meier curves and log-rank tests and subsequently using Cox proportional hazards models. Individuals withdrawn from the study early will be censored at the date of withdrawal. Specific subgroup analysis of major outcomes will be carried out, stratifying by age, sex, delirium medical subgroup and delirium risk as per the prediction of delirium in ICU patients (‘PRE-DELIRIC’) score. A fully specified statistical analysis plan will be finalised and approved by statisticians at the two main hospitals before the database is unlocked and opened. Data analysis is to be carried out using the R software programme [50].

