Patients will be assessed for delirium on enrolment. This will not be possible where patients arrive at the unit ventilated and heavily sedated. Because of this, true incidence will not be able to be established, and it is recognised that some patients may already have delirium on enrolment. The investigators feel it is important to keep this a pragmatic trial. The decision to mandate that patients be enrolled within 48 h of their ICU admission was made to ensure that the study drug is given early in patients’ stay.

The enrolment of patients who have an expected LOS longer than 72 h is being done because patients with increased LOS are more likely to develop delirium. Although prediction tools for delirium do exist [55, 56], they are complex, and we seek to maintain the generalisability of our findings to a broad range of ICU patients.

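### Randomisation is stratified by site, but the primary Mann-Whitney test is unstratified and no analysis names site: the test is valid, but conservative if sites differ

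*Protocol article*

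**What the plan says.** All references are to the protocol article.

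- **Allocation, randomisation, compliance and blinding:** 1:1 allocation from a "computer-generated randomisation list, stratified by site, with standard block sizes of six". Site is the only stratification factor.
- **Statistical methods:** "The primary endpoint, percentage of delirium-free assessments, will initially be analysed using a Mann-Whitney" U test comparing the two arms. A supporting negative binomial model then adjusts for number of assessments and, where this is thought appropriate, for important covariates and baseline data. Neither site nor enrolment delirium status is named. The same section says: "Baseline data will be recorded and analysed for imbalances between the treatment groups".
- **Prevalence of delirium** and **Discussion:** delirium at enrolment is measured only where it can be, because patients who arrive ventilated and heavily sedated cannot be assessed. The Discussion adds that "it is recognised that some patients may already have delirium on enrolment".
- **Sample size:** the calculation uses a mean of 54% delirium-free assessments with SD 45%, "aiming to detect a 10% increase in the percentage of delirium-free assessments", and a 15% allowance for a non-parametric test. It concludes: "with an alpha value of 0.05 and a power of 80%, a total of 850 patients will be recruited into the study".

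**The concern.** Blocking within site forces the arms to be nearly balanced at every site, so differences between sites largely cancel out of the treatment comparison. An unstratified rank test does not recognise this. Its null variance still contains the between-site spread, so the test behaves as if the comparison were noisier than it is. The true type I error then falls below 5% and some power is lost. Differences between ICUs in case mix, sedation practice or CAM-ICU scoring would all have this effect.

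This is not a detail left to a later analysis plan, because the article itself fixes the primary test. Enrolment delirium status is a second, weaker issue. It is a plausible predictor of later assessments, but the supporting model does not commit to using it.

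**Working it through.** **1. The plan's own sample size reproduces.** Inputs are from the Sample size section: difference 10 points, SD 45 points, two-sided α 0.05, power 80%.

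- The t-based two-sample calculation gives 318.8, so 319 per arm.
- 319 × 1.15 = 366.85 → 367.
- 367 × 1.15 = 422.05 → 423.

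With 425 enrolled per arm, the effective number is 425 × 0.85 / 1.15 = 314 or 425 / 1.15² = 321, depending on how the missing-data allowance is read. Power is then 79.5% or 80.4%. The SD is the marginal one, so 80% power was planned for the unadjusted test and is met.

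**2. Why ignoring site makes the test conservative.** Let ρ be the share of rank variance lying between sites. With arms balanced within sites, the standardised Mann-Whitney statistic has SD of about √(1−ρ) under the null instead of 1. The true type I error is about 2[1 − Φ(1.96/√(1−ρ))]. The article gives no ρ, so the values below are assumed.

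| ρ | 0.02 | 0.05 | 0.10 | 0.15 | 0.20 |
|---|---|---|---|---|---|
| true type I error | 0.048 | 0.044 | 0.039 | 0.034 | 0.028 |

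**3. Simulation check.** Assumptions: 722 evaluable patients (850 × 0.85), 12 sites, blocks of six, an outcome bounded between 0 and 1 with SD about 0.43, and 1,500 runs per scenario.

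- *Type I error, Mann-Whitney:* 0.049 with moderate site effects and 0.025 with strong ones. The simulation standard error at 0.025 is √(0.025 × 0.975 / 1500) = 0.004. In the same strong-effect runs the site-stratified test gave 0.037, itself below 0.05, so 0.025 is probably low by chance. A repeat of that scenario with 6,000 runs gave 0.037 for Mann-Whitney and 0.049 for the stratified test. This agrees with the table above.
- *Power, weak site effects:* Mann-Whitney 80.9%, van Elteren 80.6%. There is no gain, and the difference is within simulation error.
- *Power, stronger site effects:* 77.2% against 79.4%, a gain of 2.2 points. The 6,000-run repeat gave 77.1% against 78.9%. At the strongest site effect tried it gave 75.6% against 79.4%.

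**4. Baseline delirium.** If baseline covariates explain a share R² of the variance in a linear model, the SD becomes 45√(1−R²). Power is Φ(10 / [45√(1−R²)·√(2/n)] − 1.96). With n = 319:

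| R² (assumed) | 0 | 5% | 10% | 15% | 20% |
|---|---|---|---|---|---|
| power | 80% | 82% | 84% | 86% | 88% |

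The gain is therefore about 2 to 8 points over R² of 5–20%. These are linear-model figures and do not carry over exactly to a rank test or a negative binomial model. When baseline status was known in only 30% of simulated patients, a rank test stratified on the three-level status gave 76.3%, against 75.6% for Mann-Whitney. Crossing site with that status in a rank test lowered power to 73.5%, because the strata became thin.

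**The case against.** The strongest reply is that nothing here is an error. The unstratified test keeps type I error at or below 5%, and the trial is sized for it, with an allowance for a non-parametric test. Covariate adjustment is already planned as a supporting analysis, and a full statistical analysis plan is promised before the database is opened. All of that stands, and it limits the point to efficiency. It does not remove the mismatch, because the article states the primary test and that test leaves out the one factor used in randomisation.

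A reader might infer four stronger claims. The documents support none of them.

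- *Large avoidable variance, equivalent to 25% more patients.* That figure is 1/(1 − 0.20) and needs R² = 20%. The article gives no R², and baseline delirium will be unknown for many patients.
- *Bias from chance imbalance in patients already delirious at enrolment.* Under randomisation, such imbalance is already covered by the type I error of the unadjusted test.
- *Covariates chosen by imbalance testing.* The article plans to examine imbalances and, separately, to adjust where appropriate. It does not say that the first decides the second.
- *Precision already paid for through baseline delirium.* Only site is a stratification factor, so the argument applies to site alone.

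**Conclusion.** The point holds as a minor mismatch between design and analysis. The primary result would be valid and the planned power stands; what is given up is possible extra power. Under assumed site effects, the true type I error of the primary test ranges from close to 5% down to about 2.5–4%. Stratifying by site gains about 0 to 3 points of power, and just under 4 at the strongest site effect tried. With weak site effects it costs essentially nothing.

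These sizes rest on an assumed number of sites and assumed between-site variation, neither of which the article gives. The benefit of adjusting for enrolment delirium is more uncertain. It depends on unknown predictive strength and on the proportion assessable, and it would accrue to the supporting model, not to the primary test.

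**What to change.** 1. Make the primary test a site-stratified rank test (van Elteren), keeping the two-sided 5% level.
2. In the supporting adjusted model, name in advance site and enrolment CAM-ICU status as negative, positive or unassessable. The third category gives every patient a value and avoids dropping those sedated at enrolment. Enter site and status as separate terms; do not cross them as strata in the rank test.

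No new data are needed. The cost is a little extra analysis and a change to the protocol's primary-analysis wording. The Ethics and dissemination section sends protocol amendments to the ethics committees, so this is slightly more than an edit to the analysis plan. It must be made before the database is opened. The sample size need not change.

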## Background

Delirium is a state of acute organic brain dysfunction with fluctuating disturbances of attention and cognition which occurs as a direct consequence of an underlying medical condition [1]. It is particularly common in patients in intensive care units (ICUs), with a wide range of prevalence ranging between 11% and 83% reported in the literature [2–5]. Researchers in a multi-centre study that included one of the participating hospitals of this trial reported a delirium prevalence of 45% [5], whereas a preliminary audit for this trial at the two primary sites demonstrated a delirium prevalence of 52% when evaluating patients with an expected ICU length of stay (LOS) of more than 24 h.

Delirium in intensive care is associated with worse outcomes. These include higher mortality (estimated as a 10% increase in the relative risk of death for each day of delirium) [6–10], more time on a ventilator [9–11], unplanned removal of tubes and catheters [10], increased use of physical restraints [11], increased requirement for tracheostomy, greater post-operative complications [12], poorer functional status, cognitive impairment [7, 9, 13, 14], increased hospital and ICU LOSs [8, 11, 12], increased medical costs [15], higher risk of dementia [7, 13] and greater likelihood of admission to residential care [7].

The aetiology of delirium is multi-factorial [16]. In the critical care setting, it is likely that disturbances of sleep and of the normal circadian rhythm play a significant role [17]. Sleep deprivation may occur as a result of environmental disturbances, loss of normal day-night routine, critical illness itself and patient treatments. However, although sleep disturbances have been demonstrated to predispose individuals to post-operative delirium, sleep problems and their relationship to delirium in ICU remain relatively unexplored [18, 19].

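### The only adjusted model named for the primary endpoint, a negative binomial, does not fit a bounded proportion, and with its usual standard errors it would often miss the planned effect

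*Protocol article*

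**What the plan says.** Under Statistical methods, the protocol article tests the percentage of delirium-free assessments with a Mann-Whitney U test. It then states: "Subsequent supporting analyses will be carried out using a negative binomial model with adjustments made for number of assessments (accounting for withdrawals"). The same sentence lets the model adjust for baseline values and other covariates as well. No other adjusted model is named for this endpoint, and no form of standard error is given. A full statistical analysis plan is promised before the database is opened; it is not available here.

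Under Sample size, an audit of 100 patients found "an average of 54% of assessments were deemed delirium-free (SD 45"%), and the trial is "aiming to detect a 10% increase in the percentage of delirium-free assessments". The calculation is made "with an alpha value of 0.05 and a power of 80"%. Statistical methods adds: "All outcomes will be analysed for superiority (two-sided) and considered statistically significant at the 5% level".

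Under Background, a preliminary audit at the two primary sites "demonstrated a delirium prevalence of 52% when evaluating patients" with an expected stay of more than 24 h.

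**The concern.** The outcome is a count out of a known number of assessments. For such data the variance shrinks as the proportion approaches 0% or 100%. A negative binomial count has no ceiling, and its variance grows with the square of the mean. Entering the number of assessments as an offset or covariate scales the mean but does not impose the ceiling.

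Mann-Whitney gives no adjusted estimate, so in the protocol as written the negative binomial carries all covariate adjustment for the primary endpoint. If its standard errors are inflated, a real effect found by the primary test may be followed by an adjusted result that looks null. Changing the model at that stage would look data-driven.

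**Working it through.** **Inputs from the protocol.** Control mean 0.54 and SD 0.45; target 0.64; two-sided alpha 0.05; power 80%; 1:1 allocation ("Patients will be randomised to melatonin or placebo in a 1:1 ratio"); evaluable number per arm 367 ("Adjustment for a non-parametric test (15%) increases this to 367 per group"). **Assumed:** the number of assessments per patient. The protocol gives only twice daily for up to 14 days, so about 28 at most.

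**1. The plan's own figure.** n = 2 × (1.960 + 0.842)² × (45/10)² = 318 per group; the t-distribution version gives 319, as stated. 319 × 1.15 = 366.9 (367) and 367 × 1.15 = 422.05 (423). The 10% is therefore an absolute difference, 54% to 64%.

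**2. Shape of the outcome.** The largest SD possible at mean 0.54 is √(0.54 × 0.46) = 0.498. For a beta distribution with SD 0.45, a + b = 0.2484/0.2025 − 1 = 0.227, so a = 0.12 and b = 0.10, which is strongly U-shaped. In the simulated null data, about 30-32% of patients were at 0% and 38-42% at 100%.

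**3. Why the standard error is too large, at 10 assessments each.** Under no effect the fitted dispersion is 1.454.
- Negative binomial variance: 5.4 + 1.454 × 5.4² = 47.8. Actual variance: (10 × 0.45)² = 20.25. The ratio is 2.36.
- Model SE of the log ratio: √[2 × (1/5.4 + 1.454)/367] = 0.0945. Actual SE: √[2 × (0.45/0.54)²/367] = 0.0615.
- The 1.96 threshold therefore acts as 1.96 × 0.0945/0.0615 = 3.01, a type I error of about 0.3%.
- At 64% the fitted dispersion is 1.136 and the model SE is √[(1/5.4 + 1.136 + 1/6.4 + 1.136)/367] = 0.0844. Scaling the variance as p(1 − p), the treated SD is 0.433 and the actual SE is √[((0.45/0.54)² + (0.433/0.64)²)/367] = 0.0561. The effect is ln(0.64/0.54) = 0.170.
- Power is P(Z > (1.96 × 0.0844 − 0.170)/0.0561) = 53%. With the actual SE it is P(Z > 1.96 − 0.170/0.0561) = 86%.

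**4. Simulation.** Beta-binomial data, 367 per arm, 1,000 trials per scenario. NB = negative binomial on delirium-free counts with a log offset.

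| Assessments per patient | Mann-Whitney power | NB power, model SE | NB power, robust SE | NB type I error, model SE |
|---|---|---|---|---|
| Fixed 10 | 88% | 53% | 87% | 0.4% |
| Fixed 20 | 89% | 39% | 87% | 0.2% |
| Variable, 2-28 | 89% | 54% | 88% | 0.2% |
| Variable, longer when delirious | 87% | 52% | 86% | 0.3% |

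- Mann-Whitney type I error was 4.6-6.2%; NB with robust SE, 4-6%.
- Modelling delirious counts gave 40-55% power with model SE and 83-87% with robust SE.
- Using log(assessments) as a covariate, in the two variable patterns, gave 54% and 47% power and 0.2-1.0% type I error.
- The fitted model put 16-19% of its probability above the number of assessments made.

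**5. Other runs.**
- A separate simulation at 367 per arm gave 37% for NB with model SE, 83% for NB with robust SE, 91% for Mann-Whitney and 82% for a fractional logit with robust SE.
- Another, with lognormal stay and 600 trials, gave 54% for NB with model SE, 88% for Mann-Whitney and 87% for the fractional logit (type I error 4.7%).
- A different shape (361 per arm; 48% of patients at 100%, the rest averaging about 12%) gave NB 51-54% and Mann-Whitney 83%.

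**6. Discordant results.** The share of positive Mann-Whitney results with a non-significant NB is at least 1 − (NB power/Mann-Whitney power): 1 − 0.532/0.884 = 40% with fixed 10, 1 − 0.389/0.888 = 56% with fixed 20, and 1 − 0.37/0.91 = 59% in the 37% run. Direct counting in the lognormal run gave 39%.

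**The case against.** **The power loss comes from the variance, not the mean model.** This stands. The same negative binomial with sandwich standard errors reaches 83-88% power at 4-6% type I error. A reader might infer that any negative binomial analysis must lose power; that is not so, and the protocol does not say which standard errors will be used. The default ones cause the loss. The fit to impossible counts remains either way.

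**It is a supporting analysis.** This stands too. A reader might infer that the trial is underpowered or its primary result unsafe. The documents do not support that: the primary test is Mann-Whitney and the sample size is inflated for a non-parametric test. The model errs conservatively, so it does not add false positive claims.

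**A non-significant adjusted result is not a contradiction.** Agreed. In a check of the 361-per-arm scenario, every trial with a significant Mann-Whitney result had a rate ratio in the same direction. The harm is an unhelpful p-value and an over-wide interval.

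**The analysis plan may settle this.** It may add or replace a model, so the word only applies to the protocol article. But the model family is stated there, so this is a choice already made and not an omitted detail.

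**The ratio scale is partly preference.** Mann-Whitney does not estimate a 10-point difference either, and predictions from either regression can be standardised. This is a reason to report a standardised difference, not a separate fault.

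**Conclusion.** The point holds for a supporting analysis and should be fixed; the validity of the primary test does not depend on it. With the protocol's mean and SD, a negative binomial with model-based standard errors has type I error of about 0-1% and power of about 37-54%, against 83-91% for Mann-Whitney. About 40-60% of positive primary results would be paired with a non-significant adjusted analysis through misspecification alone.

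This rests on four things. The U-shape is inferred from the mean and SD, not stated. Assessments per patient are assumed, though the loss appeared under every pattern tried. The 52% prevalence used for one alternative shape comes from patients with expected stays over 24 h, whereas the trial enrols those expected to stay 72 h or more. The simulations contain no covariates and ignore the interim looks. Monte Carlo error is about 1.6 points near 50% power and 0.7 points near 5%.

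**What to change.** Before unblinding, replace the negative binomial with a fractional logit on each patient's proportion of delirium-free assessments, with robust standard errors. Adjust for site, which stratifies the randomisation, and for named baseline covariates. Report the standardised difference in percentage points with a 95% CI, the scale on which the trial was sized.

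Do not substitute a quasi-binomial model with plain Pearson dispersion: its type I error was 8-10% when the number of assessments varied. If the negative binomial is kept, the minimum is to specify robust (sandwich) standard errors.

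The cost is wording in the protocol or analysis plan. Standard R functions suffice, and neither data collection nor sample size changes.
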